**4.3.2 Intervention study**

**Primary endpoint:**

- Difference in mean fatigue levels on a numerical rating scale of 1 to 10 between the ferinject and placebo groups four to six weeks after study drug infusion.

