**4.5.2 Second study visit / study completion**

In order not to blur the effect of iron substitution, no whole blood, red cells, thrombocytes or plasma may be donated from the first blood donation at the screening until the final visit. The second, final visit takes place six to eight weeks after administration of the study drug (allowed time window 42 to 56 days). The participant is asked to complete the questionnaire package for a second time. In addition, the study coordinator will ask about any side effects on the study medication. Blood is then sampled and the blood count and various iron parameters are determined again. The material is frozen at -70° C. The study is now completed for the participant. If she or he wishes, a regular blood donation may be made at the end of the study.

Following this visit, the participant is informed in writing whether he or she has received the iron supplement or the placebo. In addition, the laboratory results of the first visit and the ferritin value of the second visit will be sent to the volunteer.

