**4.7 Premature study termination**

The participant can withdraw from the study at any time without giving a reason and withdraw his/her declaration of consent. In this case, no further data will be collected and all blood samples will be destroyed. However, data already collected will be included in the statistical analysis of the study. If the study drug has already been administered, a final medical examination will be performed at the request of the participant.

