**8. Power analysis and statistics**

The main endpoint of the intervention study is the difference in the mean level of fatigue on the numerical rating scale between the ferinject and placebo groups four to six weeks after infusion of the study drug. Based on empirical values from the literature, a standard deviation of the fatigue values of 2.5 points can be assumed. A mean difference of one point on the scale is considered clinically relevant.

200 subjects per group lead to a power of >95% to detect such a reduction with a two-sided α error of 0.05. For a secondary analysis this number of cases leads to a power of about 85% to detect a statistical interaction of the treatment effect with a subgroup in the order of 1.5 points. The primary stratification criterion will be the ferritin value at baseline (<25 µg/l versus ≥25 µg/l). Secondary stratification criteria will be sex and fatigue at baseline (<4 versus ≥4 on the numerical rating scale).

The mean values on the numerical rating scale will be compared by means of covariance analysis between the groups corrected for baseline value of the numerical rating scale. For stratified analyses we will perform an interaction test using least squares regression models. All analyses will be performed according to the intention-to-treat principle, including all randomized patients in the group to which they were initially randomized. Any missing values are replaced by multiple imputation. In a sensitivity analysis only subjects with complete data are included. All P-values are two-sided. The data analysis is performed under blind conditions, i.e. the statistician in charge will not know which of the two groups analysed received iron and which placebo. All analyses are performed in Stata Release 11 (StataCorp, College Station, TX).

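### The only sensitivity analysis for missing fatigue scores is complete-case analysis, which does not relax the imputation's missing-at-random assumption and so cannot show robustness to outcome-dependent loss

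*Protocol*

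**What the plan says.** The primary endpoint (section 4.3.2) is the "Difference in mean fatigue levels on a numerical rating scale of 1 to 10 between the ferinject and placebo groups" at one visit after the infusion. Section 8 has the means "compared by means of covariance analysis between the groups corrected for baseline value of the numerical rating scale", on an intention-to-treat basis "including all randomized patients in the group to which they were initially randomized".

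Two sentences in section 8 deal with missing data: "Any missing values are replaced by multiple imputation", and "In a sensitivity analysis only subjects with complete data are included". The protocol states no imputation model, no missing-data assumption, no expected drop-out rate, and no analysis that departs from missing at random.

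Two features of conduct matter here. Fatigue is scored at the first visit and once more at the final visit, where "The participant is asked to complete the questionnaire package for a second time" (section 4.5.2). If a participant withdraws from the study and withdraws consent, section 4.7 says "In this case, no further data will be collected and all blood samples will be destroyed", while data already collected stay in the analysis.

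**The concern.** A sensitivity analysis is informative when it relaxes an assumption on which the primary analysis depends. Here the untestable assumption is that, given what was observed, people without a final score resemble those with one. Complete-case analysis does not relax it.

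The layout sharpens the point. Someone who misses the final visit leaves a baseline score but no later fatigue score to inform the imputation. The endpoint is self-rated, and section 4.6 expects slightly more side effects on iron than on placebo. If people on iron who felt worse were more often missing, both analyses would favour iron, and their agreement could be reported as robustness.

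**Working it through.** **1. The plan's own figure.** Inputs from section 8: 200 per group, a 1-point difference, two-sided 0.05, and "a standard deviation of the fatigue values of 2.5 points can be assumed". SE = 2.5 × √(2/200) = 0.25. Power = Φ(1/0.25 − 1.96) = Φ(2.04) = 0.979, which agrees with the stated value above 95%. The power statement is not in question.

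**2. What each analysis assumes for a missing final score.**
- Complete-case covariance analysis: missingness is unrelated to the final score, given arm and baseline score.
- Standard multiple imputation: missingness is unrelated to the final score, given everything in the imputation model. That model contains at least arm and baseline, and perhaps other variables.

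The complete-case assumption is the same (arm and baseline only) or stricter (auxiliaries used).

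**3. Simulation.** Assumed, not in the protocol: baseline–outcome correlation 0.5 and roughly 10–12% missing outcomes. Used throughout: 400 participants, SD 2.5, true effect −1, 20 imputations.

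(a) 10% loss per arm, imputation from arm and baseline only, lost iron participants worse than predicted by a fixed amount, 400 trials per row:

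| Shift (points) | Complete case | Imputation | All randomised |
|---|---|---|---|
| 0 | −0.991 | −0.991 | −0.994 |
| 1 | −1.003 | −1.002 | −0.905 |
| 2 | −1.000 | −0.998 | −0.812 |

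(b) Missingness generated by different mechanisms, 800 trials per row. Negative bias favours iron:

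| Missingness in the iron arm depends on | Auxiliary in imputation | Complete-case bias | Imputation bias | SD of difference |
|---|---|---|---|---|
| Baseline score | no | −0.010 | −0.011 | 0.018 |
| Unseen final score | no | −0.178 | −0.179 | 0.016 |
| Unseen final score | yes | −0.171 | −0.113 | 0.046 |
| Auxiliary only | yes | −0.164 | −0.008 | 0.058 |

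Without auxiliaries the two methods coincide whether or not they are biased. With a strong auxiliary they separate, but the gap does not give the bias. In the third row the gap is 0.06 while imputation is still off by 0.11. In the fourth row the gap is 0.16 and imputation is essentially unbiased.

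**4. Size.** If a fraction p of one arm is missing and those people differ by δ from their imputed values, the difference moves by p × δ.

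| Loss p | δ = 1 point | δ = 2.5 points (1 SD) |
|---|---|---|
| 5% | 0.05 | 0.125 |
| 10% | 0.10 | 0.25 |
| 20% | 0.20 | 0.50 |

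If both arms are shifted, the movement is p₁δ₁ − p₀δ₀, so equal loss with equal shifts cancels.

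**5. Where a conclusion would change.** With correlation 0.5 the adjusted SD is 2.5 × √0.75 = 2.165. With loss p in each arm, SE = 2.165 × √(2/(200(1 − p))), and the tipping shift in one arm is about (|estimate| − 1.96 × SE)/p.

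| Loss p | SE | 1.96 × SE | Tipping shift, estimate −1.0 | Tipping shift, estimate −0.6 |
|---|---|---|---|---|
| 5% | 0.222 | 0.435 | 11.3 | 3.3 |
| 10% | 0.228 | 0.447 | 5.5 | 1.5 |
| 20% | 0.242 | 0.474 | 2.6 | 0.6 |

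The estimate of −0.6 is illustrative. On a 1–10 scale no shift can exceed 9 points, so 11.3 cannot be reached.

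**The case against.** The strongest objection is that this is detail for a statistical analysis plan, which may exist and is not shown. The imputation model and further missing-data scenarios commonly belong there, and no finding is made of their absence. But the protocol does choose a sensitivity analysis, and that choice can be judged on its own. A later plan could add to it without making the named check more informative.

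A reader might infer that the complete-case analysis tests nothing, or that it must reproduce the imputed result. The documents do not support that. Near-identity requires imputation from arm and baseline only, and the protocol does not say so. It collects ferritin and other iron parameters, several psychometric scales, and at the final visit a perceived-change scale. Someone who attends but leaves the fatigue item blank could be imputed from that visit's other answers, while complete-case analysis drops them. What stands is narrower: neither agreement nor a gap shows whether the primary estimate is biased by outcome-dependent loss.

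A reader might also infer from section 4.7 that participants who feel worse after the infusion are systematically lost. That section covers only withdrawal from the study with withdrawal of consent. Treatment is one supervised infusion (section 13.2), so there is no continuing treatment to abandon, and feeling worse does not itself end follow-up. Section 4.6 also judges the excess of side effects too small to affect blinding. Differential loss is possible; the documents do not predict it.

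Finally, the effect may be small. At an estimate of −1.0 with 10% loss, only a shift of about 5.5 points would remove significance. That is correct, and it limits the weight of the point.

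**Conclusion.** The point holds in a limited form. The sole named check does not relax the assumption behind the primary analysis, so it cannot support a claim that the result is robust to loss depending on the unseen fatigue score. This follows from the structure of the two methods and needs no assumed drop-out rate.

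The size does rest on assumptions: 5–20% loss, baseline correlation 0.5, and departures of 1 to 2.5 points in one arm. These give movements of 0.05 to 0.50 points. A clear 1-point effect would survive most of that range. An effect nearer the boundary, about 0.45 points at 10% loss, might not. Nothing here shows that the primary analysis is invalid or that the trial is underpowered. It is a cheap improvement.

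**What to change.** Keep the complete-case analysis, labelled supplementary, and add a pre-specified delta-adjusted analysis to section 8 or the statistical analysis plan:

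- Impute as planned, then add a fixed shift to the imputed final fatigue scores in one coded arm, then in the other, then in both. Working with coded arms matters because section 8 keeps the statistician unaware of which group received iron.
- Extend the shifts until the conclusion changes or the limits of the 1–10 scale are reached. A short grid, such as 0.5 to 2 points, would miss the tipping point in the main scenario above (about 5.5 points).
- Report the tipping point with the number missing in each arm and any reasons given.

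The cost is a few lines of Stata, one table, and a shift range that must be chosen before unblinding. Design, sample size and burden on participants do not change.

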**9. Study specific precautions**

The study drug is generally well tolerated. Higher degree side effects are rare. Special precautions are not indicated after administration of the study medication. When the participants continues to feel well, driving is not prohibited after administration of the study medication. If side effects occur after administration of the study medication, the participants are requested to contact the donor physician at the Blood Donation Centre Bern immediately or, in an emergency, an emergency doctor. After administration of the study medication, the participant is given an information sheet with contact details.

**9.1 Pregnancy**

There is no evidence of embryonic or fetal toxicity of iron carboxymaltose. However, in the absence of data, administration during the first trimester is contraindicated. For this reason, a urine pregnancy test is performed in every woman of childbearing age (menarche to confirmed menopause). If the result is positive, the volunteer cannot be included in the study. Electronic randomisation for the study is only possible after a negative result of the pregnancy test has been entered into the eCRF and validated.

A serum pregnancy test is not practical in the planned study setting. Since the early pregnancy risk of iron carboxymaltose can be considered very low (no pregnancy complications due to iron carboxymaltose were reported two years after market approval) and a urine test, if performed correctly, detects pregnancy in >99% of cases, the safety of a urine pregnancy test is sufficiently guaranteed. It can also be assumed that urine pregnancy tests are generally carried out in medical practice before Ferinject® is administered.

The medication information approved by Swissmedic does not give any recommendation as to how long after the administration of the medication a conception must be avoided. In everyday clinical practice, therefore, contraception is not necessarily ordered after administration of Ferinject®. Iron carboxymaltose is very rapidly absorbed into the macrophages of the reticulo-endothelial system, where it is broken down into iron hydroxide and sugar components. The elimination half-life in blood is 7 to 12 hours^28^. After this time, iron is bound to transferrin and ferritin, which prevents toxic effects.

Based on the above considerations, study participants of childbearing age must commit themselves to a minimum of three weeks of anti-conception after administration of the study medication. If no permanent anti-conception (mechanical or medication-based) is performed, mechanical methods (e.g. condoms) must be used for three weeks. No anti-conception measures are indicated for female partners of male study participants.

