**7.5 Pregnancy**

Every woman of child-bearing age has to undergo a urine pregnancy test before enrolment. Pregnant women cannot be included in the study. All women of childbearing age are required to prevent conception for at least three weeks. If no permanent (medicinal or mechanical) contraception is used, temporary contraception with a mechanical method (condom) is required.

At the second study visit, specific questions are asked as to whether a pregnancy has become known in the meantime (a pregnancy test is not carried out). If this is the case, the outcome of the pregnancy will be inquired from every woman after she has given birth and the outcome is recorded in the eCRF.

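### The only safeguard before the infusion is one same-day urine test, and contraception is required only afterwards, so a very recent conception can be infused (minor, cheap to close)

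*Protocol*

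**What the plan says.** Section 9.1 states that "in the absence of data, administration during the first trimester is contraindicated", and gives this as the reason for testing every woman of childbearing age. The test is a hard gate: "Electronic randomisation for the study is only possible after a negative result of the pregnancy test" has been entered and validated. By section 4.5.1 the test is done at the first study visit. By section 13.2 the infusion is given that same day.

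Section 9.1 discusses the choice of test. It says "A serum pregnancy test is not practical in the planned study setting", that "a urine test, if performed correctly, detects pregnancy in >99% of cases", and that "the early pregnancy risk of iron carboxymaltose can be considered very low". It also reports no sign of embryonic or fetal toxicity, gives an elimination half-life of 7 to 12 hours, and says that the iron is bound after that.

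The contraception rule appears twice. Section 7.5 says "All women of childbearing age are required to prevent conception for at least three weeks" and gives no starting point. Section 9.1 supplies one: "study participants of childbearing age must commit themselves to a minimum of three weeks of anti-conception after administration of the study medication".

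At the second visit no test is done. By section 7.5, "specific questions are asked as to whether a pregnancy has become known in the meantime", and any pregnancy is followed to its outcome.

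**The concern.** The stated aim is to keep the drug away from the first trimester. A pregnancy test can find only a pregnancy that has become detectable. A woman who conceived a few days before the visit would test negative and pass the gate. Contraception in the preceding days would cover that interval, but the protocol asks for it only from the infusion onwards.

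The participants are healthy donors, and section 11.2 sees no proven advantage in either arm, so an avoidable exposure has no offsetting benefit. What is at stake is the safety of a small number of women. The fatigue comparison is not affected.

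**Working it through.** The plan gives no figure on this point to reproduce. The check is a comparison of the sections, followed by simple date arithmetic.

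**1. What each measure covers, by time of conception**

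| Conception | Measure in the protocol | Prevents exposure? |
|---|---|---|
| Long enough before visit 1 to be detectable | Urine test gating randomisation (4.5.1, 9.1) | Yes |
| Before visit 1, not yet detectable | None required | No |
| Within three weeks after the infusion | Contraception (7.5, 9.1) | Yes |
| Any, once known by visit 2 | Question and outcome follow-up (7.5) | No, records it only |

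The second row is the gap. It exists for any undetectable interval longer than zero. The detection figure in 9.1 does not close it, because it gives no time since conception, and correct performance of the test cannot reveal a pregnancy that is not yet detectable.

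**2. Contraception after compared with before**

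Three weeks are 21 × 24 = 504 hours. With the half-life of 7 to 12 hours in 9.1, that is 504 / 12 = 42 to 504 / 7 = 72 half-lives. The protocol thus asks for caution well beyond the drug's stated time in the blood, and for none in the days before the infusion.

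**3. Age of a missed conception at visit 2**

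Inputs: visit 2 falls 42 to 56 days after the infusion (4.5.2). The undetectable interval is assumed to be up to 14 days, so a missed conception is 0 to 14 days old at the infusion.

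- Youngest: 42 + 0 = 42 days (6 weeks)
- Oldest: 56 + 14 = 70 days (10 weeks)

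Many such pregnancies would be known by then, but the exposure would already have happened.

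**4. Number affected**

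The protocol gives neither the number of women of childbearing age nor their contraceptive use. For illustration only: expected number = women × share without contraception × conception probability per cycle × 0.5, where 0.5 stands for an undetectable interval of about half a cycle. All inputs are assumed.

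- Low: 100 × 0.05 × 0.01 × 0.5 = 0.025
- Middle: 200 × 0.20 × 0.05 × 0.5 = 1.0
- High: 300 × 0.40 × 0.20 × 0.5 = 12

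Allocation is 1:1 and the placebo is saline (4.5.3, 4.6), so half of each figure would meet iron: 0.0125, 0.5 and 6. The high case combines extreme inputs. The spread (12 / 0.025 = 480-fold) means that this is not an estimate. It shows only that the number need not be zero.

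**5. Room to postpone**

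Visit 1 lies four to six weeks after the donation (4.5.1), that is day 28 to day 42, a width of 14 days. The room left from day d is 42 − d: 14 days from day 28, 7 from day 35, 0 from day 42. A request for 14 days of contraception before visit 1 must reach the woman between day 28 − 14 = 14 and day 42 − 14 = 28 after the donation, depending on the booking.

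**The case against.** The strongest reply is that 9.1 makes a reasoned choice. It compares urine with serum testing, judges the early-pregnancy risk very low, cites an absence of reported pregnancy complications two years after approval, and notes that everyday practice does not necessarily order contraception even after the drug. The contraindication rests on missing data and not on observed harm. The length of the undetectable interval is not in the protocol. The participant information was not available for review, so advice there about the time before the visit cannot be excluded.

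Most of this stands, and it is why the point is minor. It does not explain why contraception is required for three weeks after the infusion and not at all before it. The risk judgement lowers the stakes of a missed conception but does not make the gate catch one.

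A reader might infer more than the text supports:

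- **That the protocol overlooks pregnancy.** It does not. It excludes pregnant women, blocks randomisation until a negative test, and follows outcomes.
- **That 7.5 and 9.1 contradict each other.** They do not. Section 7.5 leaves the start open and 9.1 fixes it.
- **That substantial harm or many exposures are to be expected.** Nothing in the protocol shows this. Women already using permanent contraception are protected, and about half of any missed conceptions would meet only saline.

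**Conclusion.** The point holds as a minor safety improvement. With the plan followed exactly, a conception too recent for the urine test can be infused, although 9.1 contraindicates first-trimester administration. The expected harm is small on the protocol's own account, and the number of women cannot be derived. The existence of the gap rests on one item of general knowledge, that a pregnancy test has some interval in which it cannot detect a conception. The assumed 14 days affect only the age at visit 2 (42 to 70 days) and the length of contraception proposed before the visit.

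**What to change.** 1. State in both 7.5 and 9.1 that women of childbearing age use contraception from before visit 1 until three weeks after the infusion.
2. Ask for this in the existing telephone invitation and mailed information. It can only be a request at that stage, because consent is signed at visit 1.
3. At visit 1, before randomisation, apply one criterion next to the negative urine test: contraception or abstinence either since the last menses or for at least the preceding 14 days (the assumed interval). Meeting either part is enough, so a woman who did what she was asked cannot fail.
4. If the criterion is not met, postpone the infusion within the four-to-six-week window or do not enrol. Section 13.2 then needs a matching sentence, since it ties the infusion to the day of consent.
5. In 9.1, limit the detection figure to pregnancies advanced enough to be detectable.

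The cost is wording in these sections and the participant information, plus one eCRF item. The downside is that a few women are rescheduled or not enrolled. A full 14-day postponement fits only from day 28, so the telephone request matters more than discovery at the visit.
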